## Abstract

**Background and purpose:**

Research to date has lacked definitive evidence to determine whether mirror therapy promotes the recovery of upper extremity function after stroke. Considering that previous studies did not stratify patients based on structural retention, this may be one of the reasons for the negative results obtained in many trials. The goal evaluates the efficacy of TBMT (utilizing an innovatively designed mirror) versus standard occupational therapy for stroke patient’s upper limb functionality.

**Methods and analysis:**

This single-center randomized controlled trial will involve 50 patients with stroke. All patients will be randomly assigned to either the task-based mirror therapy or the control group. The interventions will be performed 5 days per week for 4 weeks. The primary outcomes will be the mean change in scores on both the FMA-UE and modified Barthel Index (MBI) from baseline to 4 weeks intervention and at 12 weeks follow-up between the two groups and within groups. The other outcomes will include the Action Research Arm Test (ARAT), the Nine Hole Peg Test (9HPT), the Functional Independence Measure, and MRI.

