### Sample size estimation

The sample size was derived from pre-existing research using G Power v.3.1, considering significance level (*α*) = 0.05, power (1 − β) = 0.95, and given that the minimal clinically significant difference in patient’s hand function improvement, as per prior study data, is 9 points in the FMA-UE with an effect size of *d* = 1.13 [14]. Estimation via G Power software yielded a requirement of 44 samples. Considering potential subject attrition or termination, the sample size could be augmented by 10–15%, resulting in the adjusted sample size of *N* = 50, or 25 patients in each group. Consequently, the total sample size for both groups was formulated as 50.

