#### Primary outcomes

The Fugl-Meyer Assessment for upper extremity (FMA-UE) will be utilized to evaluate the level of upper limb motor function impairment, with a maximum score of 66 points [28, 29]. This assessment includes 23 different movements grouped into four categories (shoulder/elbow/forearm, wrist, hand/finger, and coordination), whereby 33 items are assessed. Rated on a 3-point scale, task completion is scored as 0 for inability, 1 for partial ability, and 2 for near-normal ability. The reliability, validity, and responsiveness of the FMA-UE assessment for stroke patients are well recognized [30]. Therefore, FMA-UE will be considered as the primary outcome.

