#### Secondary outcomes

Brunnstrom is a motor function and muscle spasticity assessment method for the affected upper extremity [31]. It includes six stages: Grade 1: absence of random movement, no upper or lower extremity movement; Grade 2: joint response, comovement, and minimal random movements; Grade 3: random comovement with the ability to grasp but not extend; Grade 4: separation of movement, including the ability to pinch and make minor extensions; Grade 5: gradual restoration of muscle tone with fine movements, simultaneous yet independent extension of fingers; and Grade 6: motor ability approaching normalcy but speed and accuracy are suboptimal.

The Modified Barthel Index (MBI) assesses the mobility of stroke patients concerning their ability to carry out specific activities of daily living. These activities include eating, bathing, dressing, bowel and urinary control, toileting, bed and chair transfer, level walking, and stair walking [32, 33]. A total score of 100 can be achieved, and scores of 60 or higher indicate self-sufficiency. Independence positively correlates with the score.

We commonly use the Action Research Arm Test (ARAT) to assess the ability of the affected upper extremity and hand to handle objects of different sizes, weights, and shapes. The test assesses 19 tests of arm motor function, both distal and proximal. Each test is given a score of 0, 1, 2, or 3, with higher scores resulting in better function. The total ARAT score is the sum of the 19 tests, resulting in a maximum score of 57 [34]. Nine Hole Peg Test (9HPT): assesses the patient’s whole hand dexterity. The assessment requires the patient to take nine pegs from the container and insert them into a small pegboard, then remove and place them back into the container. The patient’s score depends on the speed of insertion and removal, with the faster the time, the higher the score [35].

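### The abstract and the body name different primary outcomes, and no primary time, contrast or multiplicity rule is fixed for the clinical outcomes

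*Protocol article*

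**What the plan says.** The article gives two current and incompatible definitions of the primary outcome.

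- **Abstract, Methods and analysis.** "The primary outcomes will be the mean change in scores on both the FMA-UE and modified Barthel Index (MBI"), measured "from baseline to 4 weeks intervention and at 12 weeks follow-up between the two groups and within groups". That is two scales, two times and two kinds of contrast.
- **Primary outcomes.** Only FMA-UE is described: "Therefore, FMA-UE will be considered as the primary outcome".
- **Secondary outcomes.** The MBI appears here: "The Modified Barthel Index (MBI) assesses the mobility of stroke patients".
- **Sample size estimation.** The calculation uses FMA-UE alone (9 points, d = 1.13), "considering significance level (*α*) = 0.05, power (1 − β) = 0.95". Then: "Estimation via G Power software yielded a requirement of 44 samples". This is raised to 50 for attrition.
- **Statistical analysis.** FMA-UE, MBI, ARAT and 9HPT all go through the same mixed ANOVA with four time levels. A separate FMA-UE regression is placed four weeks after treatment stops. Any p below 0.05 counts as significant. The section does not say which scale, time or contrast decides the trial, and it gives no order of testing and no adjustment for the clinical outcomes.

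**The concern.** A reader cannot tell which result would make this trial positive. Under the abstract, a difference on either scale at either time might count, and so might a change within one arm. Under the body, only FMA-UE counts, but its time is still open. The stated power belongs to a single FMA-UE comparison at 5%, so it does not describe the abstract's set of outcomes. If the choice is left until the data are seen, it can be made to suit them.

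The within-group wording is a separate problem. Patients enter 1 to 6 months after stroke, and both arms receive 40 minutes of therapy on each treatment day. Both arms can therefore improve without any effect of TBMT, so a change within the TBMT arm does not address the superiority objective given under Study design.

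**Working it through.** **1. The plan's own figure.** Inputs from Sample size estimation: d = 1.13, alpha 0.05, power 0.95. Allocation is 1:1 (Study design). For a two-sided two-sample t-test, the noncentrality is d × √(n/2).

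- n = 22 per arm: 1.13 × √11 = 3.75 on 42 degrees of freedom, power 0.956. This is the smallest n that reaches 0.95, so the total is 44 and the stated figure is reproduced.
- A one-sided test would need only 18 per arm, so the figure is two-sided.
- Attrition: 44 / 0.88 = 50.
- n = 25 per arm: 1.13 × √12.5 = 4.00, power 0.975.

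The calculation is sound for one FMA-UE comparison.

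**2. If any one between-group test suffices.** With k independent tests at 5%, the false-positive rate is 1 − 0.95^k.

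- k = 2: 1 − 0.9025 = 9.75%
- k = 4: 1 − 0.8145 = 18.5%

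The documents give no correlations. Assumed ranges were therefore simulated (25 per arm, 40,000 runs per setting): 0 to 0.7 between scales and 0.5 to 0.9 between times.

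| Tests that could each count | False-positive rate |
|---|---|
| Two scales, one time | about 8–10% |
| Two scales, two times | about 12–17% |
| FMA-UE only, two times | about 7–9% |

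The last row shows that adopting the body's definition alone is not enough; the time must be fixed as well.

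**3. If the abstract's set were kept and Bonferroni-controlled.** FMA-UE power, assuming d = 1.13 at each time:

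| Tests | Alpha each | Power, 22 per arm | Power, 25 per arm | Evaluable total for 95% |
|---|---|---|---|---|
| 2 | 0.025 | 0.918 | 0.950 | 50 |
| 4 | 0.0125 | 0.866 | 0.914 | 58 |

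**4. If both scales had to succeed.** Alpha does not inflate. Joint power cannot exceed the FMA-UE power of 0.956 at 22 per arm, only about half a percentage point above 0.95. No MBI effect or SD is given, so the loss cannot be fixed. As an illustration, an MBI test of equal power and independent of FMA-UE gives 0.956 × 0.956 = 0.914; positive correlation would bring this closer to 0.956.

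**5. Within-group change.** Suppose TBMT adds nothing and both arms recover by g SDs of change (assumed). The paired t-test in the TBMT arm has noncentrality g × √25 = 5g on 24 degrees of freedom.

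| g | Chance that the TBMT pre-post test is significant |
|---|---|
| 0.25 | 22% |
| 0.5 | 67% |
| 1.0 | 99.8% |

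**The case against.** The strongest reply is that the body settles the matter. FMA-UE is the primary outcome, the sample size agrees with it, and the abstract is loosely worded. A separate analysis plan may also hold the hierarchy. The agreement with the sample size stands, and it is why the repair is cheap. But the abstract is current text that says something else, and an unseen plan cannot make both statements true.

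Several stronger readings are tempting, and the documents do not support them.

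- **The false-positive rate is above 5%.** This holds only if any one success is claimed. The article states no such rule, and the abstract's wording about both scales could mean that both are required. A single group-by-time test in the ANOVA could also merge the times within one scale, though the text speaks of differences at each time.
- **Every test is run at 5% without correction.** This is true of the clinical outcomes. The functional connectivity maps receive an AlphaSim correction.
- **A large chance that only one arm is significant.** With an assumed recovery of 3 to 5 points, 22 per arm, and 9 / 1.13 = 7.96 taken as the SD of change, the within-arm test is significant with probability 0.39 to 0.80. The chance that exactly one arm is significant is then 48% to 32%, but half of that is control-only. The TBMT-only pattern is 0.39 × 0.61 = 24% at 3 points and 0.80 × 0.20 = 16% at 5, falling to 7% at 6. The article does not say that 7.96 is a change SD and gives no recovery figure.
- **A within-arm test is planned for the clinical scales.** The statistical section names none; the only paired t-tests are for imaging. The within-group route rests on the abstract's wording.
- **The Functional Independence Measure is never assessed.** The abstract lists it and the readable outcome and analysis text does not describe it, but the schedule in Table 2 is not visible here.
- **The registry entry is out of line.** It cannot be seen, so nothing can be said of it.

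**Conclusion.** The contradiction is explicit and should be corrected before unblinding. The abstract makes FMA-UE and MBI primary at two times, between and within groups; the body makes FMA-UE alone primary, and the trial was sized for that.

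The size of the problem depends on how success would be claimed. With any single between-group success, the error rate is about 8–10% (two scales, one time) to about 12–17% (two scales, two times), given the assumed correlations, with 18.5% as the independence figure. With both scales required, the cost falls on power instead, and it cannot be quantified without an MBI effect. The within-group figure of about 67% rests on an assumed common recovery of 0.5 SD. The principle does not depend on that figure: a pre-post change in one arm is not an estimate of the treatment effect.

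**What to change.** 1. State one primary endpoint in the abstract, outcome, sample-size and analysis sections: the between-group difference in FMA-UE at one named time, adjusted for baseline. The end of the 4-week intervention is one candidate.
2. Reconcile that time with the FMA-UE regression in Statistical analysis, which is set four weeks after treatment ends, and say which model gives the primary result. Study design and Outcome measurements also describe the visits differently and should be brought into line.
3. Make MBI and the other time points secondary, either tested in a fixed order after the primary or reported with confidence intervals.
4. Remove the within-group contrast from the primary outcome and label within-group change descriptive.
5. Minor: check the Functional Independence Measure against Table 2, then either describe it among the secondary outcomes or drop it from the abstract.

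The cost is wording. The sample size of 44 evaluable, 50 in total, stands, because it was calculated for one FMA-UE test at 5%. The small downside is that MBI can no longer carry a primary claim.

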**Discussion:**

This trial will not only to establish that task-based mirror therapy (TBMT) could improve the recovery of hand function after stroke but also to explore the underlying mechanisms. We expect that this finding will clarify the brain activation and brain network mechanisms underlying the improvement of hand function with task-oriented mirror therapy and lead to new ideas for stroke hand function rehabilitation.

**Trial registration:**

URL: https://www.chictr.org.cn; Unique identifier: ChiCTR2300068855. Registered on March 1, 2023

**Supplementary Information:**

The online version contains supplementary material available at 10.1186/s13063-024-08081-1.

## Introduction

The severe consequences of stroke often result in residual motor, sensory, cognitive, urinary, and fecal dysfunction, making it challenging for survivors to reintegrate into their families and society [1, 2]. Recent research indicates that approximately 85% of stroke patients experience hemiparesis in their upper or lower extremities, while 55 to 75% of stroke survivors face limited upper extremity function [3]. Upper extremity function accounts for 60% of total body function, and hand function alone comprises 90% of upper extremity function. Therefore, effective hand rehabilitation is essential to successfully reintegrate patients into their families and enhance their independence [4].

Although rehabilitation training is the primary treatment method for stroke patients, the current results of rehabilitation for poststroke hand dysfunction are not satisfactory [1]. There is an urgent need to develop more effective and inexpensive rehabilitation techniques for hand function. Mirror therapy (MT) has emerged as a promising new rehabilitation intervention in recent years [5, 6]. MT typically involves placing a flat mirror on the unaffected side of the body, allowing the patient to “embody” their paralyzed limb through the optical illusion created by the mirror. This technique effectively “tricks” the brain into perceiving movement in the affected limb, potentially aiding in the recovery of motor function. MT has shown particular efficacy in the treatment of phantom limb pain [7–9] and has also begun to show promise as a therapeutic approach for stroke [5]. Research has demonstrated that MT is an effective adjunctive therapy for improving upper extremity motor function and daily living among stroke patients [7, 10–12]. A study found that MT combined with bilateral arm training and graded activities was effective in improving motor performance of the paretic upper limb after stroke compared with conventional therapy without MT [13]. We have also done previous studies demonstrating that the combination of conventional rehabilitation therapy and TBMT is an effective way to improve functional recovery in upper limb stroke patients [14] (Fig. 1). However, to date there has been little agreement on the facilitative effect of MT. A randomized controlled trial by Antoniotti et al. found no significant difference between actual and sham MT for functional recovery of the upper extremity in early stroke [15]. There is a strong link between acquisition of motor skills and neuronal plasticity at cortical and subcortical levels in the central nervous system [16]. Therefore, it is possible that these limitations arise from the fact that patients exhibit varying degrees of structural preservation at the injury site, and the treatment of MT effect on upper limb motor function of hemiplegia is somehow dependent on the severity of the lesion, which ultimately resulted in contradictory findings.

**Fig. 1 Fig1:**
[figure not shown]
Conventional mirror therapy

The corticospinal tract (CST) is the primary descending motor pathway that connects cortical motor regions with spinal cord neurons, and it plays a crucial role in human upper limb mobility. Consequently, maintaining the structural integrity of the CST is crucial for determining the upper limits of upper limb recovery in patients. Studies have shown that the extent of CST injury is the optimal biomarker for successful rehabilitation of the upper extremity after stroke [17]. Baseline anatomical integrity assessment is essential to ensure patient balance and uniformity. Furthermore, this approach can predict functional recovery in chronic stroke for more effective neurological rehab treatment. Because there is a significant correlation between functional recovery and the preserved structural basis of the lesion [18]. Diffusion tensor imaging (DTI) is an MRI imaging technique that can detect lesions and display nerve fiber bundles in three dimensions [19]. Previous research has established that extracting CST bundle FA values from DTI data can yield valuable insight into their integrity and provide useful information about individualized rehabilitative strategies in stroke patients [20]. For this study, in an attempt to ensure the consistency of treatment efficacy irrespective of patient disease characteristics, we will employ DTI to assess the severity of CST degeneration in our subject patients. Post-enrollment, we will conduct a subgroup analysis to ensure balanced rehabilitation potential across various patient populations.

On the other hand, imaging evaluation can also help us understand the mechanisms by which mirror therapy [21–23]. For example, during MT, stroke patients showed increased functional magnetic resonance imaging (fMRI) activities across widely distributed brain regions [24, 25]. Camera-based visual input from the start-up mirror facilitated motor recovery, daily functioning, and brain network separation in subacute stroke patients [26]. However, few authors have been able to provide a systematic account of the mechanisms of mirror therapy. This new clinical trial is unique due to the following factors: the innovative utilization of DTI imaging which considers CST integrity as a fundamental measure, reduces variables that may impact the randomization process; the implementation of a novel therapeutic apparatus that improves the effectiveness of TBMT; to investigate the mechanism, the project proposes to use the BOLD-fMRI technique to reflect the active level of brain regions and whole-brain functional network connections to reveal the spontaneous activity patterns, connectivity patterns, and brain network characteristics, thus providing new theoretical support for the study of the neural mechanisms of mirror therapy.

## Methods/design

### Study design

This is a single-center, prospective, single-blinding, randomized controlled superiority trial. The objective will be used to evaluate the effectiveness of TBMT (using a newly designed mirror) compared to conventional occupational therapy on upper extremity functions of stroke patients. Patients will be randomly allocated in a 1:1 ratio into a control (*N* = 25) or TBMT group (*N* = 25), with the control group receiving conventional occupational therapy intervention and TBMT group receiving task-based mirror therapy in addition to CG. A professional team will measure relevant outcomes at baseline and 4 weeks after treatment.

### Sample size estimation

The sample size was derived from pre-existing research using G Power v.3.1, considering significance level (*α*) = 0.05, power (1 − β) = 0.95, and given that the minimal clinically significant difference in patient’s hand function improvement, as per prior study data, is 9 points in the FMA-UE with an effect size of *d* = 1.13 [14]. Estimation via G Power software yielded a requirement of 44 samples. Considering potential subject attrition or termination, the sample size could be augmented by 10–15%, resulting in the adjusted sample size of *N* = 50, or 25 patients in each group. Consequently, the total sample size for both groups was formulated as 50.

### Participants

Fifty eligible patients with upper limb motor dysfunction in stroke will be recruited from the outpatient and inpatient departments of the Department of Rehabilitation Medicine, Department of Neurology, and Department of Neurosurgery of the Second Hospital of Chongqing Medical University. Eligible patients had to satisfy the inclusion, exclusion criteria, and termination criteria (Table 1). Information about this trial will be posted via posters in the waiting area of the Rehabilitation Department and the Rehabilitation Medicine Clinic so that interested patients can contact the program director through their therapist. If an applicant meets the study criteria, then they will be invited to participate

**Table 1 Tab1:** Inclusion, exclusion criteria and termination criteria

**Inclusion criteria** 1. Meet the diagnostic criteria for stroke (including cerebral hemorrhage and cerebral infarction) formulated by the 4th National Cerebrovascular Disease Conference in 1995and confirmed by head CT or MRI, and the course of the stroke is 1 to 6 months 2. Abnormal hand function after stroke, Brunnstrom stage I-III, upper limb FMA-UE score lower than 47 3. The contralateral hand is in good condition 4. The age of the patient is 20-80 years old, and the gender is not limited 5. No progressive stroke performance, stable vital signs 6. Cognitive function is relatively intact, MMSE>17 or MoCA>24 7. Be able to follow the clinical treatment plan and sign the subject's informed consent
**Exclusion criteria** 1. Subjects with upper limb dysfunction before stroke 2. Subjects with visual impairment or unilateral neglect 3. Severe cognitive impairment or poststroke depression 4. Metal implants in the body, such as cardiac pacemakers and other metal devices 5. Suffering from serious underlying diseases, such as heart function level 4 (NYHA) or severe COPD 6. Subjects participating in other clinical trials at the same time 7. Subjects judged to be unsuitable for this trial, and withdrawing voluntarily 8. Subjects unable to undergo MRI scans
**Termination criteria** 1. Subjects have serious adverse events or adverse reactions 2. Subjects have other changes in their condition and cannot continue the trial 3. Subjects have significant problems in the design of the protocol or the trial and are unable to determine the efficacy

### Randomization and blinding

A total of 50 patients who meet the inclusion criteria will be randomly assigned to either the task-based mirror group or the control group. The randomization sequence will be generated by an independent statistician using SPSS Version 19.0. Patients will be assigned randomization numbers based on the order of enrollment. To maintain blinding, opaque sealed envelopes will be utilized to conceal group assignments. Patients will only become aware of their group after opening the envelope, which will be securely stored in a separate cabinet. Blinding of evaluators will be employed in this study to avoid bias stemming from subjective factors. The same investigator, who will be blinded to the treatment assignment, performed all the assessments. Additionally, statisticians will conceal the groupings and their significance, and the code will remain undisclosed until the analysis is finalized. In case of a severe incident during a trial, blinding may need to be undone for proper treatment. This decision must be endorsed by the trial’s lead researcher/medic, and recorded in the protocol, with utmost consideration given to minimizing bias and ensuring data quality.

